### 3.17 Hospitalization/Inpatient Monitoring

---

During dose escalation, each subject should be hospitalized the nights prior to C1D1 and C1D8 for hydration, treatment with uric acid-reducing agents, and monitoring. The subject may be discharged once TLS labs are reviewed 24 hours after dosing. See Protocol Section 6.2 for further detail.

Subjects in Japan will be hospitalized for the duration of the DLT period (see Section 5.1).

### 3.18 Dispense Study Drug

---

ABBV-467 will not be directly dispensed to subjects. Study drugs will be administered to subjects beginning at baseline (Day 1) and as specified in Section 2.1. The first dose of study drugs will be administered after all other baseline (Day 1) procedures are completed.

Each site will be responsible for maintaining drug accountability records including product description, manufacturer, and lot numbers for all non-investigational products dispensed by the site.

The first dose of ABBV-467 on C1D1 will be administered at half the targeted dose for a given subject; subsequent doses will be administered at the full target dose. ABBV-467 will be administered weekly, for each 28-day cycle, over at least a 30-minute period at approximately the same time each day, with or without food. Alternative dose schedules and infusion times may be explored pending adequate accumulation and thorough review (including with investigators) of clinical safety and PK data.

### 3.19 Subject Withdrawal from Study

---

All attempts must be made to determine the date of the last study drug dose and the primary reason for discontinuation of study drug or study participation. The information will be recorded on the appropriate eCRF page. However, these procedures should not interfere with the initiation of any new treatments or therapeutic modalities that the investigator feels are necessary to treat the subject's condition. Following discontinuation of study drug, the subject will be treated in accordance with the investigator's best clinical judgment, irrespective of whether or not the subject decides to continue participation in the study.

## 4 SAFETY MANUAL

### 4.1 Methods and Timing of Safety Assessment

---

All serious and nonserious AEs which could be related to study procedures (e.g., occurrence during screening) will be collected from the time the subject signed the study-specific informed consent until study drug administration and reported to the sponsor. From the time of study drug administration until 30 days after discontinuation of study treatment, all AES and SAEs will be collected whether solicited or spontaneously reported by the subject.

[figure not shown]

AE = adverse event; SAE = serious adverse event

## 4.2 Recording Data and Analyses of Safety Findings

Adverse events will be coded using MedDRA. The number and percentage of subjects with treatment-emergent adverse events (i.e., any event that begins or worsens in severity after initiation of study drug through 30 days post-study drug dosing) will be tabulated by primary MedDRA SOC and preferred term and compared between arms using Fisher's exact test. The tabulation of the number of subjects with treatment-emergent AEs by severity grade and relationship to study drug also will be provided. Subjects reporting more than 1 AE for a given MedDRA preferred term will be counted only once for that term using the most severe grade according to the severity grade table and the most related according to the relationship to study drug tables. Subjects reporting more than 1 type of event within an SOC will be counted only once for that SOC.

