## 4 INVESTIGATIONAL PLAN

### 4.1 Overall Study Design and Plan

---

This is a Phase 1, first-in-human, open-label, dose escalation and dose expansion study evaluating ABBV-467 in subjects with R/R MM and R/R AML; the schematic of the study is shown in [Figure 1](#). Further details regarding study procedures are located in the Operations Manual. See [Section 5](#) for information regarding eligibility criteria. Dosing will be weekly, on a 28-day cycle, though alternative

dosing frequencies may be studied if supported by the totality of safety, efficacy, PK, and/or pharmacodynamic (PD) data.

Subjects will continue ABBV-467 therapy until disease progression, unacceptable toxicity, or withdrawal of consent. No subject will receive ABBV-467 for longer than 24 months within the context of this study.

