### Choice of Control Group

Not applicable.

---

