## 5.8 Randomization/Drug Assignment

This is an open-label study; there is no randomization. As they are enrolled in the study, subjects will be assigned unique identification numbers. At the time of screening, assignment of unique subject numbers and dose assignments will be done via interactive response technology. For subjects who rescreen, the screening number assigned at the initial screening visit should be used.

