### Analysis of Adverse Events

Analyses of AEs will include only treatment-emergent events. The number and percentage of subjects experiencing treatment-emergent AEs will be tabulated according to the primary Medical Dictionary for Regulatory Activities (MedDRA) system organ class (SOC) and MedDRA preferred term. Subjects reporting more than 1 AE for a given MedDRA preferred term will be counted only once for that term. Subjects reporting more than one type of AE within a MedDRA SOC will be counted only once for that SOC. Subjects reporting more than one type of AE will be counted only once in the overall total.

SAEs, drug-related AEs, AEs leading to death, dose interruption and dose modification as applicable, study treatment discontinuation, and study discontinuation will be summarized using the same methods as described above.

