## 7.6 Multiplicity Adjustment and Overall Type I Error Control

---

Not applicable.

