## 7.7 Sample Size Determination

---

A total of approximately 108 subjects will be enrolled in this study. In the dose-escalation component, the number of subjects will depend upon the occurrences of DLT events as specified in the allocation rules for BOIN design. Including a minimum of 6 subjects treated during dose escalation at what is ultimately declared the RP2D, it is estimated that approximately 30 subjects each will be treated in Part A and Part C (approximately 60 total).

The expansion component will target enrollment of 20 response-evaluable subjects (with a maximum of 24 subjects enrolled regardless of response evaluability) each into Parts B and D (up to 48 enrolled total) to further evaluate the safety profile, and preliminarily evaluate efficacy, of ABBV-467 at RP2D. Subjects will be considered response-evaluable if they have received at least 1 dose of ABBV-467 and have died, or exited the study due to progressive disease, or had at least 1 post-baseline response assessment per the indication-specific response criteria. Subjects who die or exit for progressive disease, prior to their first baseline assessment, will be considered to have not responded to the therapy.

With a sample size of 24 subjects, the probability to observe at least 1 occurrence of AE is  $\geq 92\%$  if the true incidence of the respective AE rate is  $\geq 10\%$ .

No formal hypothesis testing is planned for this first-in-human study; preliminary assessment of efficacy is a secondary objective of this study. [Table 5](#) provides the lower bound of a one-sided 80% CI corresponding to various observed response rates assuming a total of 20 response-evaluable subjects in each cohort. For example, if a 25% response rate is observed, the lower bound of a one-sided exact CI will exclude 15% (or lower) rates of response, providing some preliminary assessment of efficacy.

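### The Operations Manual prescribes Fisher's exact tests of adverse events between arms, but the study defines no arms and its statistical section plans only descriptive tabulation

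*Protocol*

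**What the plan says.** Operations Manual Section 4.2 (Recording Data and Analyses of Safety Findings) defines treatment-emergent adverse events and orders counts and percentages by system organ class and preferred term. It then adds that these are to be "compared between arms using Fisher's exact test". It gives no significance level or sidedness and does not say what an arm is.

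The body of the protocol describes something different:

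- Section 4.1: "This is a Phase 1, first-in-human, open-label, dose escalation and dose expansion study evaluating ABBV-467 in subjects with R/R MM and R/R AML". Every subject receives the same agent.
- Section 4.2 (Discussion of Study Design): the entry under "Choice of Control Group" is that the item does not apply.
- Section 5.8: "This is an open-label study; there is no randomization".
- Section 7.5 (Analysis of Adverse Events): "The number and percentage of subjects experiencing treatment-emergent AEs will be tabulated according to the primary" MedDRA system organ class and by preferred term. No comparison or test follows. The same section groups subjects for safety by the treatment they received.
- Section 7.6: the entry under "Multiplicity Adjustment and Overall Type I Error Control" is likewise that it does not apply.
- Section 7.7: "No formal hypothesis testing is planned for this first-in-human study".

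**The concern.** The Operations Manual is Appendix J of the protocol, and Section 8.2 requires the study to be conducted in accordance with it. The clause is therefore current, operative text. An analyst who follows it departs from Section 7.5, and one who follows Section 7.5 departs from the clause.

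This differs from a detail left to the statistical analysis plan. The protocol positively names a test, and it names it for groups that do not exist. To carry it out, someone would have to choose the groups, possibly after seeing the data.

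Safety is a primary objective. A table of p-values beside the adverse event counts invites two misreadings: that a large p-value between tiny cohorts shows similar toxicity, and that a small one among many untouched by any error control shows a real difference.

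**Working it through.** **1. The plan's own figures, and whether the clause enters them.**
- Section 7.7 sizes safety by detection: the chance of at least one event in 24 subjects at a true rate of 10% is 1 − 0.9^24 = 0.920, which matches the stated 92%.
- Enrolment is 30 + 30 in Parts A and C plus 24 + 24 in Parts B and D = 108, as stated.
- Neither figure uses a between-group test. Escalation follows the BOIN decision table in Section 4.1 together with clinical review, and expansion follows a cumulative data review. None of these uses a p-value.

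**2. The texts side by side.** Operations Manual 4.2 and Protocol 7.5 describe the same table (subjects with treatment-emergent events, by system organ class and preferred term). They differ in that 4.2 adds a comparison. Sections 4.1, 4.2 and 5.8 of the protocol supply no arms for it: one agent, no control group, no randomization. The candidate groups are dose levels, the two diseases, and the escalation and expansion parts. None is called an arm or assigned to this test.

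**3. What the test would give for groups one might invent.** The groupings below are illustrations; the protocol orders none of them. A two-sided 0.05 level is assumed, because none is stated.

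*Small dose cohorts.* Section 4.1 lets escalation decisions rest on 2 DLT-evaluable subjects at dose levels 1 and 2 and on 3 at later levels. For n versus n with all events in one group, the two-sided Fisher p-value is 2 / C(2n, n).
- 2 versus 2: 2 / C(4,2) = 2/6 = 0.33.
- 3 versus 3: 2 / C(6,3) = 2/20 = 0.10.
- 6 versus 6: 2 / C(12,6) = 2/924 = 0.0022.

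At the two smallest sizes significance is impossible whatever the toxicity. At 6 versus 6 it is possible, but only from 0 against 5 events upward when one group has none.

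*Part B versus Part D at the maximum of 24 each.* For 0 versus k events, p = 2 × C(24,k) / C(48,k).
- k = 4: 2 × 10,626 / 194,580 = 0.109.
- k = 5: 2 × 42,504 / 1,712,304 = 0.0496.

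So 0 versus 5 is the smallest split from zero that reaches 0.05. Power for true rates of 10% versus 30% is about 31%. Such a comparison would also be confounded by disease, and possibly by dose, since the Synopsis allows the recommended dose to differ between the two diseases.

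*Many terms.* With an assumed 20 independent preferred terms, each at a nominal 0.05, the chance of at least one false positive is up to 1 − 0.95^20 = 0.64. Fisher's test is conservative: at 24 versus 24 and a common event rate of 30% its actual size is 0.026, which gives 1 − 0.974^20 = 0.41.

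**The case against.** The strongest reply is that the clause is harmless. It reads like carried-over template text, it identifies no comparison that could be run as written, and nothing in the conduct of the trial depends on it. This largely stands, and it limits the weight of the point. It does not rescue the clause, because no feature of the design supports it.

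Several stronger readings are tempting, and the documents do not support them:

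- *That Section 7.7 rules out any test of adverse events.* It excludes formal testing, in a sentence that goes on to efficacy and leads into the response-rate table. A descriptive p-value is not strictly barred by it, and the not-applicable entry in Section 7.6 could fit unadjusted descriptive output. The firm conflict is with Section 7.5 and with the absence of arms.
- *That the clause orders dose-cohort or myeloma-versus-leukemia comparisons.* It orders neither; both are illustrations used here.
- *That the possible groups are never concurrent.* Part C opens once an active and tolerable dose is found in Part A, not once Part A has closed, and nothing prevents Parts B and D from enrolling together.
- *That all groups are tiny.* Escalation allows up to 12 subjects at a dose level and expansion up to 24 per cohort. The 3 versus 3 case is close to the worst.
- *That this is a single-arm trial in the usual sense.* The protocol does not use that term. There are several dose levels and two diseases; uncontrolled and single-agent is the more exact description.

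**Conclusion.** The point holds as an internal contradiction. Operations Manual 4.2 prescribes a between-arms test in an uncontrolled, non-randomized, single-agent study that defines no arms and whose statistical section plans descriptive tabulation of adverse events only. This conclusion comes from reading the sections together and rests on no numerical assumption.

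The figures show only why the output would not be interpretable. The minimum p-value of 0.10 at 3 versus 3 is exact; calling it non-significant assumes a 0.05 level. The 31% power and the 41% to 64% false-positive chances also depend on the assumed event rates and number of terms.

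The consequence is confined to how safety would be reported. A reader might infer that dose selection or sample size is at risk, but neither depends on the clause. It should be corrected because safety is a primary objective and the correction is simple.

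**What to change.** In Operations Manual Section 4.2, strike the words "compared between arms using Fisher's exact test" together with the conjunction that introduces them. Keep the rest of the section: the definition of treatment-emergent events, the tabulation by grade and relationship, and the rule for counting each subject once. State that the tabulation is descriptive and, as in Protocol Section 7.5, groups subjects by treatment received. Grouping by assigned dose level would create a new inconsistency with that section.

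Confidence intervals for selected event rates in the expansion cohorts would be an optional addition. Neither Section 7.5 nor Section 7.7 calls for them, and they are not needed to resolve the contradiction.

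The cost is one deleted clause and a short alignment. Planned enrolment stays at about 108 and the detection probability stays at 92%.

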## 4.3 Reporting Adverse Events and Intercurrent Illnesses

In the event of an SAE, whether associated with study drug or not, the investigator will notify Clinical Pharmacovigilance within 24 hours of the site being made aware of the SAE by entering the SAE data into the electronic data capture system. SAEs that occur prior to the site having access to the RAVE® system, or if RAVE is not operable, should be documented on the SAE non-eCRF and emailed (preferred route) or faxed to Clinical Pharmacovigilance within 24 hours of the site being made aware of the SAE.

Email: [[contact]](mailto:[contact])

FAX to: [contact]

[figure not shown]

For safety concerns, contact the Oncology Safety Team at:

AbbVie Oncology Safety Team, [name]  
[name]  
[name]  
Office: [contact]  
Email: SafetyManagement\[contact]

For any subject safety concerns, please contact the physician listed below:

**[contact]**

The sponsor will be responsible for Suspected Unexpected Serious Adverse Reactions (SUSAR) reporting for the Investigational Medicinal Product (IMP) in accordance with Directive 2001/20/EC.

## 5 COUNTRY-SPECIFIC REQUIREMENTS

### 5.1 Japan-Specific Information

**Study Design:**

*Special Populations*

At least 1 Japanese subject will be enrolled at each dose level in dose escalation Parts A and C. Subjects from sites in Japan will be enrolled sequentially, and will be incorporated into the BOIN dose escalation decisions as they become DLT-evaluable. In Parts B and D (dose expansion), at least 3 Japanese subjects are planned to be enrolled.

## Hepatitis B virus (HBV) testing

In Japan, if hepatitis B surface antigen (HBsAg) is negative at screening, hepatitis B surface antibody (HBsAb) and hepatitis B core antibody (HBcAb) should be tested to ensure the safety of the subject. If HBsAb and/or HBcAb is positive and hepatitis B virus (HBV) DNA value is < 2.0 IU/mL, monitoring should be conducted following monitoring method described in Figure 1.

**Figure 1. Guidelines for the Prevention of Hepatitis B Virus Reactivation in Subjects Receiving Immunosuppressive Therapy or Chemotherapy**

[figure not shown]

ALT = alanine aminotransferase; AST = aspartate aminotransferase; HBc = hepatitis B core; HBs = hepatitis B surface; HBsAg = hepatitis B surface antigen; HBV = hepatitis B virus; NA = nucleos(t)ide analog

Addendum: Caution is required when administering powerful chemotherapeutic agents for hematological malignancies, as during or following completion of treatment some HBsAg positive or negative patients will develop hepatitis B due to reactivation of HBV, and some of these will go on to suffer fulminant hepatitis. Consideration should also be given to the possibility of HBV reactivation in association with standard chemotherapy for hematological malignancies or solid cancers, and immunosuppressive therapy for autoimmune diseases, such as rheumatic and collagen diseases. The incidences of HBV reactivation, hepatitis and fulminant hepatitis associated with standard chemotherapy and immunosuppressive therapy are not known, and there is a lack of evidence on which to base guidelines. Furthermore, prevention of fulminant hepatitis is not guaranteed with NA therapy.

NB 1) HBV carriers and patients with resolved hepatitis B should be screened prior to immunosuppressive therapy or chemotherapy. First HBsAg testing should be performed to determine whether they are an HBV carrier. HBsAg negative patients should be tested for anti-HBc antibody and anti-HBs antibody, to confirm past infection. Highly sensitive testing

methods should be used for measurements of HBsAg, anti-HBc antibody and anti-HBs antibody. Even for only anti-HBs antibody positive patients (i.e., HBsAg negative and anti-HBc antibody negative), reactivation of HBV has been reported, so the action should be taken in accordance with the guidelines unless there is evidence of prior vaccination to HBV.

NB 2) A hepatologist should be consulted concerning HBsAg positive patients. A hepatologist should preferably be consulted for all patients administered NAs.

NB 3) In some patients undergoing retreatment who did not undergo testing for anti-HBc or HBs antibody at the time of their initial chemotherapy, and in patients who have already commenced immunosuppressive therapy, antibody titers may be low, in which case measurement of HBV DNA levels is preferable.

NB 4) Patients with resolved HBV infection should be screened using real-time PCR measurement of HBV DNA levels.

NB 5)

- a. Caution is required when treating patients with resolved HBV infection with rituximab + corticosteroid or fludarabine chemotherapy, or when they undergo hematopoietic stem cell transplantation, as these patients are at high risk of HBV reactivation. HBV DNA levels should be monitored on a monthly basis during treatment, and for at least 12 months afterward. Long-term monitoring is required for hematopoietic stem cell transplant recipients.
- b. Although the incidence is low, there is a risk of HBV reactivation with standard chemotherapy regimens and combination with molecular targeted therapy with immune-activity. HBV DNA levels should be measured every 1 – 3 months, with the interval and duration tailored to the individual therapy regimen. It is best to err on the side of caution with patients undergoing treatment for hematological malignancies.
- c. There is also a risk of HBV reactivation associated with immunosuppressive therapy using corticosteroids, immunosuppressant agents, or molecular targeted therapy with immunosuppressant or immunomodulator activity. HBV DNA levels should be monitored on a monthly basis in patients on immunosuppressive therapy for at least 6 months after commencement or alteration (including cessation) of treatment. After 6 months, the interval and duration should be tailored to the individual therapy regimen.

NB 6) Administration should be commenced as soon as possible, before commencement of immunosuppressive therapy or chemotherapy. However, for HBsAg positive patients with high HBV load, it should be reduced prior to initiation of immunosuppressive therapy or chemotherapy, because fatal cases have been reported due to fulminant hepatitis even on NA therapy.

NB 7) Administration should be commenced as soon as the HBV DNA levels exceed 2.1 log copies/mL, during or after immunosuppressive therapy or chemotherapy. If this occurs during treatment, it is preferable to consult with a hepatologist, and not immediately cease the immunosuppressant or antineoplastic agent with immunosuppressive activity.

NB 8) Entecavir is the recommended NA.

NB 9) Cessation of NA therapy can be considered if the following criteria are met. In patients who were HBsAg positive at the time of screening, when the criteria for cessation of NA therapy in cases with chronic hepatitis B are met. In patients who were anti-HBc antibody and/or anti-HBs antibody positive at the time of screening:

- (1) NA therapy has been continued for at least 12 months after completion of immunosuppressive therapy or chemotherapy.
- (2) ALT (GPT) levels have been normalized during this period (excluding causes of elevated ALT levels other than HBV).
- (3) negative conversion of HBV DNA has occurred during this period.

NB 10) Patients should be carefully monitored, including measurement of HBV DNA levels, for at least 12 months following completion of NA therapy. Monitoring methods depend on package inserts of each NA. NA therapy should be immediately resumed if HBV-DNA levels exceed 2.1 log copies/mL during monitoring period.

Cross reference: Drafting Committee for Hepatitis Management Guidelines and the Japan Society of Hepatology.

